# Neuroprotective effects of exercise in people with progressive multiple sclerosis (Exercise PRO-MS): study protocol of a phase II trial

**DOI:** 10.1186/s12883-020-01765-6

**Published:** 2020-05-11

**Keywords:** Progressive multiple sclerosis, Exercise, High intensity interval training, Progressive resistance training, Neurodegeneration

## Abstract

**Background:**

Neurodegeneration, rather than inflammation, plays a key role in the progressive phase of multiple sclerosis (MS). Current disease modifying treatment options for people with progressive MS (PMS) do not specifically target neurodegeneration. Preliminary evidence suggests that exercise therapy might have neuroprotective effects. However, neuroprotective effect studies of exercise interventions in PMS are scarce and the possible mode of action underlying neuroprotective effects of exercise are unknown and need to be elucidated. The main aim of this phase II trial is to assess whether progressive resistance training (PRT) and high intensity interval training (HIIT), can slow down neurodegeneration in people with PMS.

**Methods:**

In a single-blinded phase II clinical trial with an extended baseline period, 60 people with PMS will be randomly assigned to PRT or HIIT. The participants should have had a relapse onset of MS with confirmed disease progression, however still ambulatory. The duration of the study is 48 weeks, consisting of 16 weeks baseline period (no intervention), 16 weeks intervention and 16 weeks follow-up. Patient-tailored training will be performed 3 times per week for one hour in groups, led by an experienced physiotherapist. The primary outcome measure is neurodegeneration, measured as whole brain atrophy on magnetic resonance imaging (MRI). Secondary outcome parameters will include other biomarkers associated with neurodegeneration (i.e. regional brain atrophy, lesion load, white matter integrity, resting state functional connectivity, blood biomarkers (brain derived neurotrophic factor (BDNF) and serum neurofilament light (sNFL)), patient functioning (physical and cognitive) and cardiovascular risk factors.

**Discussion:**

Besides the primary outcome measures, this study will examine a large variety of biomarkers associated with neurodegeneration after an exercise intervention. Combining outcome parameters may help to elucidate the mode of action underlying neuroprotective effects of exercise.

**Trial registration:**

This trial is prospectively registered at the Dutch Trial Registry (number NL8265, date 06-01-2020).

## Background

Multiple sclerosis (MS) is a complex disease of the central nervous system (CNS), with inflammatory and neurodegenerative aspects [1]. According to Lublin et al. MS can be categorized in different clinical subtypes, namely active versus not active neuroinflammation, with or without progression [2]. Progressive MS (PMS) is characterized by a gradual deterioration of daily activities due to increasing neurological symptoms [3]. The underlying pathophysiological mechanism for this deterioration is still poorly understood although it is known that neurodegeneration (i.e. axonal and neuronal loss in the CNS) plays a prominent role in PMS [1, 3]. Neurodegeneration is not yet targeted by the available disease modifying therapies (DMTs). These interventions generally target neuroinflammation [1, 3]. Some preliminary evidence from animal models, healthy aging individuals and people with MS suggests that exercise might have a neuroprotective effect [4–7].

### Exercise and neurodegeneration

Animal studies on the effects of exercise, demonstrated that endurance training in a mouse model of MS, i.e. experimental autoimmune encephalomyelitis (EAE), resulted in a better structurally preserved nervous system [4]. The endurance exercise group showed less severe motor impairment and autopsy showed less dendritic loss and less synaptic defects, compared to a sedentary mouse group [4].

Also, in healthy people research on the neuroprotective effects of exercise has been conducted. These studies suggest a neuroprotective effect of exercise and physical activity. Endurance training conducted at a moderate-to-vigorous intensity for six months resulted in an increase in grey- and white matter volume, especially in the prefrontal and temporal cortices [5]. Additionally, moderate intensity endurance training can upregulate levels of brain derived neurotrophic factor (BDNF) in healthy aging individuals [8, 9]. BDNF is a neurotrophin which plays an important role in synaptic plasticity, neuronal survival, differentiation and neuronal growth, and levels of BDNF decrease in neurodegenerative diseases [9–11]. Moreover, BDNF is strongly linked to cognitive functions [12, 13].

In people with MS exercise has been widely adopted as an intervention for patient functioning and general well-being. Exercise guidelines recommend twice weekly resistance training and endurance training to improve cardiorespiratory fitness, muscle strength, daily functioning and quality of life [14–16]. Cross-sectional functional MRI data indicate that people with MS who are more physically active (determined as averaged movement counts per day measured with an accelerometer) have increased resting state functional connectivity (rsFC) in the default-mode network (DMN) [17]. rsFC, measured with functional MRI, is a measure of the blood-oxygen-level-dependent signal used to examine the functional architecture of the brain [18]. The functional architecture of the brain in people with MS generally differs from that of healthy controls, and correlates with MS severity as measured by the Expanded Disability Status Scale (EDSS) [19]. In people with MS decreased rsFC of the DMN is associated with a decreased cognitive functioning [20, 21].

A recent systematic review indicated that 2–3 times exercise per week for at least 4 weeks can improve brain function and brain integrity in people with MS [6]. A 24-week progressive resistance training (PRT) intervention study in people with relapsing remitting MS, showed a trend towards brain preservation in the training group. A slowing of the natural loss of brain volume, expressed as percentage brain volume change (PBVC) was found of − 0.01%, (95% confidence interval (95%CI): − 0.15 to 0.13) compared to a PBVC of − 0.28, (95%CI: − 0.61 to 0.06) in the waitlist control group [7]. In addition, a better cardiorespiratory fitness is associated with a better integrity of the nervous system and larger (deep) grey matter brain volumes, except for the thalamus [22, 23]. Intervention studies in MS also examined the effect of exercise on rsFC. A 4-week intervention study combining endurance and resistance training demonstrated increased rsFC in the sensorimotor brain network areas [24]. The sensorimotor network plays an important role in motor function and rsFC in the sensorimotor network is decreased in people with MS [25]. Likewise, after a task-oriented walking intervention rsFC increased between sensorimotor areas [26]. An endurance walking intervention in people with MS demonstrated an improved rsFC between thalamic and right superior frontal gyrus, and thalamic and left medial frontal gyrus, associated with better cognitive performance [27]. In addition, white matter microstructural integrity measured with Diffusion Tensor Imaging (DTI) may improve with exercise [28]. Also in MS, an upregulation of BDNF after moderate intensity endurance training has been demonstrated [6, 11, 29, 30].

Exercise is a safe intervention for people with MS and current guidelines recommend exercise and physical activity to people with MS, because of the beneficial heath effect on patient functioning and cardiovascular risk [14, 31]. Exercise might be effective to reduce the cardiovascular risks associated with inactivity [15, 32]. The above-mentioned studies do indicate that exercise in people with MS has a positive effect on neurodegeneration. However, sample sizes in previous studies were small (N varying from 8 to 61), the content, frequency, intensity, and duration of exercise interventions differed, and outcome measures were heterogeneous (brain volume measures, rsFC, DTI-parameters, neuronal growth- and neurotrophic factors) [6]. Furthermore, there were no studies that examined the effect of exercise on neurodegeneration specifically in the relapse-onset PMS population. So, at this point the effects of different exercise interventions on neurodegeneration in the PMS population are not known.

### Exercise PRO-MS

In the proposed Exercise PRO-MS study an extensive set of neurodegenerative biomarkers will be used to investigate the effect of two patient-tailored exercise programs, i.e. PRT and high intensity interval training (HIIT) on neurodegeneration in people with PMS. Both resistance and endurance training might affect neurodegeneration but currently it is unknown whether one intervention is more beneficial than the other one. In the proposed study we will examine the effectiveness of both interventions on neurodegeneration in the PMS population.

The primary aim of this trial is:

To examine whether PRT and HIIT can slow down neurodegeneration in people with PMS. We expect that participants will benefit from both PRT and HIIT as compared to no training.

Additional objectives of the Exercise PRO-MS study are:
To determine whether PRT and HIIT can improve patient functioning in people with PMS.To explore the relationships between patient functioning on the one hand, and biomarkers related to neurodegeneration on the other hand.To determine the relative responsiveness of neurodegeneration outcome measures, and to explore effect sizes of between-intervention comparisons.To determine whether cardiovascular risk factors improve as a consequence of a PRT or a HIIT intervention.

## Methods/design

### Design and setting

A single-blind monocenter randomized phase II trial with extended baseline will be conducted from 2020 till 2023 at the MS Center Amsterdam (MSCA), The Netherlands. MSCA is embedded in the Amsterdam UMC, location VUmc, and is a specialized center for MS care, research and education. In an extended baseline design, participants function as their own control reducing variance and increasing power. During intake participants will be assessed for eligibility for inclusion. In case of inclusion, participants will be scheduled for two baseline measurements sixteen weeks apart. After the second baseline measurement participants will be randomized to either the PRT or HIIT group. Measurements will be repeated post-intervention and after a 16-week follow-up period.

#### Randomization and blinding

Randomization will be performed to prevent selection bias. A computer-generated variable block-randomization model will be used. Block size will be disclosed at the end of the study. Block randomization is applied to achieve an approximately equal group size over time. An independent investigator will inform the physiotherapist about allocation of participants, participants will be notified of the intervention during the first training session. The outcome assessor will be unaware of allocation, and measures will be taken to ensure her blinding during the study. The physiotherapist and participant will not be blinded, since this is not possible.

### Study population

Participants will be recruited through the MS Center Amsterdam, patient organizations and social media. People who are interested will receive a patient information letter. If people are willing to participate an eligibility check will be planned. During this intake visit in- and exclusion criteria will be checked. Prior to all measurements participants will sign the informed consent form. If participants do not meet all inclusion criteria they will be excluded from the study. Inclusion criteria for this study are [1] definite diagnosis of MS according to the 2017 McDonalds criteria, with gradual progression of neurological impairments according to the Lublin criteria 2013 for at least 2 year [2, 33], [2] age between 18 and 70 years, [3] EDSS 3.5–6.0 [34, 35], [4] able to participate in exercise (i.e. no known cardiovascular, pulmonary or metabolic disease, or symptoms of cardiovascular disease), [5] able to understand instructions, and [6] fulfilling MRI safety criteria (no metal inside the body, no claustrophobia and no pregnancy). Exclusion criteria are [1] diagnosis of primary PMS (PPMS), [2] relapse within 3 months before baseline visit, [3] severe comorbidity, objectified as a score ≥ 3 in 1 or more organ systems on the Cumulative Illness Rating Scale (CIRS) [36], [4] initiation of fampridine within 6 months of baseline, [5] severe depression, objectified as a score ≥ 11 on the Hospital Anxiety and Depression Scale (HADS) [37], [6] other neurological- and/or musculoskeletal disorders, [7] already participating in a (guided) high intensity exercise training, [8] participating in another intervention study, and [9] pregnancy, given birth in previous 6 months or an active pregnancy wish.

All study procedures will be performed in accordance with the 1964 Helsinki Declaration and its later amendments or comparable ethical standards. Written informed consent will be obtained from all individual participants.

### Withdrawal and replacement of individual participants

Participants can leave the study at any time for any reason if they wish to do so without any consequences. The investigator can decide to withdraw a participant from the study for urgent medical reasons. Participants who leave the study prior to random allocation to the exercise programs will be replaced. Participants who leave the study after random allocation will not be replaced. Participants that withdraw from the intervention will be asked to complete assessments post intervention and at follow-up. Also, they will be asked to share the reason for withdrawing from the study (Fig. 1).

**Fig. 1 Fig1:**
[figure not shown]
Participant Timeline

### Sample size calculation

Based on pre- and post-intervention measurements, paired analysis will be performed to examine the effect of exercise per type of intervention. Power calculation was performed using data from a previous study examining the effect of a 24-week progressive resistance training (group difference of 0.3 PBVC, standard deviation (SD) 0.5, estimated effect size 0.6) [7]. A sample size of 24 achieves 80% power with a significance level of 0.05. With an estimated drop-out of 15% we will include 30 participants per group.

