### Interventions

Both interventions (PRT & HIIT) will be performed three times per week for 16 weeks, supervised by a physiotherapist. Participants can start at different time points. So, group size and composition are variable. Training intensities are based on individual abilities. In case adjustments in exercises or intensities need to be made due to certain disabilities or circumstances, this will be documented and standardized.

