### Outcome measures

Measurement will take place at baseline (week 0), extended baseline (week 16), post-intervention (week 32) and at follow-up (week 48) (Table 2).

**Table 2 Tab2:** Schedule of enrollment and measurements

	**Enrollment**	**Baseline**		**Intervention period**	**Post-intervention**	
Week no:	-1	0	16	24	32	48
**Informed consent**	X					
**Screening**	X					
**Sociodemographic and clinical characteristics**		X				

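### The planning effect of 0.3 PBVC comes from a 24-week trial and is used unscaled and unjustified for 16-week intervals, so the stated 80% power is not supported

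*Protocol article*

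**What the plan says.** The Sample size calculation section of the protocol article plans a paired analysis within each exercise arm. Its inputs are borrowed: "Power calculation was performed using data from a previous study examining the effect of a 24-week progressive resistance training", with the values "group difference of 0.3 PBVC, standard deviation (SD) 0.5, estimated effect size 0.6". From these it derives 24 evaluable participants per arm for 80% power at a significance level of 0.05, and 30 per arm after allowing for 15% drop-out.

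The source is described under Exercise and neurodegeneration as "A 24-week progressive resistance training (PRT) intervention study in people with relapsing remitting MS". PBVC there was -0.01 (95% CI -0.15 to 0.13) with training and -0.28 (95% CI -0.61 to 0.06) "in the waitlist control group".

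This trial runs on a shorter clock: "Both interventions (PRT & HIIT) will be performed three times per week for 16 weeks". Outcome measures places the scans at weeks 0, 16, 32 and 48. Primary objective compares PBVC across the three resulting intervals, separately for each arm. The population is relapse-onset progressive MS. The article gives no 16-week atrophy rate, no progressive MS rate and no SD for a 16-week interval.

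**The concern.** PBVC is a change accumulated between two scans, so its size depends on how far apart they are. A difference built up over 24 weeks is not the difference to expect over 16. The borrowed 0.3 is about the whole loss that the source's untrained group showed in 24 weeks, so at that rate less than 0.3 would be lost, and could be saved, in 16 weeks.

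The 80% is the only power statement for the primary outcome. If the true figure is well below it, a null result in one arm could be read as evidence against that form of exercise, although the arm had limited ability to show even a complete halt of atrophy at the cited rate.

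**Working it through.** **Inputs.** Difference 0.3, SD 0.5, n = 24, alpha 0.05, drop-out 15% (Sample size calculation). Source PBVC -0.28 untrained and -0.01 trained over 24 weeks (Exercise and neurodegeneration). Interval length 16 weeks (Interventions; Outcome measures). Sidedness is not stated; two-sided reproduces the article's figure.

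**Reproducing the plan.** For a paired t-test, d = difference / SD, and power comes from the noncentral t distribution with n - 1 degrees of freedom and noncentrality d x sqrt(n).

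- d = 0.3 / 0.5 = 0.6; noncentrality 0.6 x sqrt(24) = 2.94; power 80.4%. The stated n = 24 is exact.
- 24 / 0.85 = 28.2, so 29; the stated 30 per arm covers it, and 30 x 0.85 = 25.5 evaluable.

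**Putting the effect on a 16-week scale** (assumptions: loss linear in time; progressive MS rate like the cited one).

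- Source difference: 0.28 - 0.01 = 0.27, given as 0.3.
- Planning difference: 0.30 x 16/24 = 0.20.
- Untrained loss, which is the gain from complete arrest: 0.28 x 16/24 = 0.187.
- For complete arrest to gain 0.3 in 16 weeks, the untrained rate would have to be 0.3 x 24/16 = 0.45 per 24 weeks, and 0.45 / 0.28 = 1.6 times the cited point estimate.

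**SD at 16 weeks.** The documents do not give it. PBVC spread mixes measurement error per scan pair, which does not depend on the interval, with between-person variation in true loss, which shrinks as the interval shortens. Three cases span the range:

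- unchanged: 0.5
- square root of time: 0.5 x sqrt(16/24) = 0.408
- fully proportional, with no fixed measurement error: 0.5 x 16/24 = 0.333

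**Power, two-sided paired t-test.**

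| 16-week effect | SD | d | Power, n = 24 | Power, n = 30 | n for 80% |
|---|---|---|---|---|---|
| 0.187 | 0.5 | 0.373 | 42% | 51% | 59 |
| 0.187 | 0.408 | 0.457 | 57% | 68% | 40 |
| 0.187 | 0.333 | 0.56 | 75% | 84% | 28 |
| 0.20 | 0.5 | 0.40 | 47% | 56% | 52 |
| 0.20 | 0.408 | 0.49 | 63% | 74% | 35 |
| 0.20 | 0.333 | 0.60 | 80% | 89% | 24 |

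**What 80% at n = 24 requires.** The 16-week ratio of effect to SD must be about 0.6. That means an effect of 0.6 x 0.5 = 0.30, 0.6 x 0.408 = 0.245 or 0.6 x 0.333 = 0.20. Relative to the cited untrained loss of 0.187, these are 1.6, 1.3 and 1.07 times.

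The paired t-test follows the article's own calculation; the planned analysis is a linear mixed model. The SD of 0.5 is taken, as the article takes it, to be that of the paired difference.

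**The case against.** The calculation itself contains no slip: n = 24 follows from d = 0.6, and quoting 0.27 as 0.3 is ordinary rounding to one decimal. The dispute is about a planning assumption. That stands.

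A reader might infer that 0.3 is more than this trial could ever show. The documents do not support that. The loss of 0.28 is one point estimate, from relapsing remitting MS, with a confidence limit of -0.61; this scales to 0.61 x 16/24 = 0.41 over 16 weeks, so a loss of 0.3 lies within the cited uncertainty. Progressive MS may lose volume faster. Nor is complete arrest a strict ceiling: the background reports volume increases after six months of endurance training in healthy people, and the source's trained arm has an upper limit of +0.13. Against this, the control interval also includes no loss (upper limit 0.06), the stated aim is to slow degeneration rather than reverse it, and the article does not argue for a faster rate.

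A reader might also infer that the SD must stay at 0.5, which would make 42% to 47% the answer. The split between measurement error and true variation is not given, so these figures are only the least favourable end of the range shown.

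Finally, it may be said that a phase II trial whose sample size would not change needs no correction. The phase II label is fair context, but the 80% is printed as the basis for the sample size and will be relied on when results are read.

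**Conclusion.** The concern holds. The article applies a 24-week between-group difference and SD from a relapsing remitting trial to a primary outcome measured over 16-week intervals, with neither rescaling nor justification. On its own cited figures, power with 24 evaluable per arm is 42% to 75% for complete arrest (0.187) and 47% to 80% for the scaled planning effect (0.20), depending on how the SD behaves. The stated 80% is reached only at the edge where there is no fixed measurement error, or if atrophy is faster than the cited point estimate or brain volume grows.

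This rests on loss being roughly linear in time and on progressive MS having a rate like the cited one; the documents establish neither. The conclusion is that the 80% is unsupported as written, not that it is shown to be unattainable.

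A further question is whether a between-group SD suits a within-person contrast of two intervals. A reader might combine the two and infer still lower power, but that depends on a correlation between intervals that the article does not give, and nothing here relies on it.

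**What to change.** In Sample size calculation, state the planning effect and its SD on a 16-week scale, with the scaling assumption for each. Alternatively, give a progressive MS atrophy rate and the reason for choosing it. Replace the single 80% with a power range for 24 to 30 evaluable per arm; the table above supplies it for effects of 0.187 and 0.20. Say that arm-specific results will be reported as phase II estimates with confidence intervals and not as an 80%-powered test.

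Keep the 60 participants; design, endpoint and analysis are unchanged. The cost is rewording and a less favourable stated power.

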### Interventions

Both interventions (PRT & HIIT) will be performed three times per week for 16 weeks, supervised by a physiotherapist. Participants can start at different time points. So, group size and composition are variable. Training intensities are based on individual abilities. In case adjustments in exercises or intensities need to be made due to certain disabilities or circumstances, this will be documented and standardized.

#### Progressive resistance training (PRT)

The PRT schedule consists of 3 exercises for the lower extremity (leg press, unilateral leg extension and unilateral hamstring curl), 2 exercises for the upper extremity (bench press and seated rows) and 1 core exercise (cable wood chop), to improve muscle strength. Intensity will be at 60–80% of participants one-repetition maximum (1RM). The training will start with a 5-min warming-up on a bicycle ergometer followed by PRT (Table 1a). The training will end with a cooling down of 5 min on a bicycle ergometer and 5 min of stretching and relaxation (see Additional file 1 TIDieR Checklist PRT).

**Table 1 Tab1:** Trainings programs, (A) progressive resistance training and (B) high intensity interval training

**A. Progressive Resistance Training**				**B. High Intensity Interval Training**				
*Week*	*Load (%1RM)*	*Volume*	*Rest (minutes)*	*Week*	*Sets*	*Interval (minutes)*	*Rest (minutes)*	*%peak heartrate*
1–2	60	3 × 12	2–3	1	5	1	1	80
				2	5	1	2	85
3–4	65	3 × 12	2–3	3	5	1	1	85
				4	5	2	2	80
5–6	70	3 × 10	2–3	5	5	2	2	85
				6	5	2	2	90
7	75	4 × 10	2–3	7	4	3	3	85
8	1RM measurement			8	Cardiopulmonary exercise test			
9–10	65	3 × 12	2–3	9	6	2	2	85
				10	4	3	3	80
11–12	70	3 × 10	2–3	11	4	3	3	85
				12	4	4	3	80
13–14	75	4 × 10	2–3	13	4	4	3	85
				14	4	4	3	90
15–16	80	4 × 10	2–3	15	5	2	2	95
				16	5	3	3	90

